### Statistical analysis

The primary statistical analyses will be conducted on an intention-to-treat basis using STATA statistical software release 12.0 (STATA, College Station, TX, USA). Per-protocol analysis will also be performed by including all participants who are at least 80% compliant in completing the exercise (as measured by the number of exercise sessions attended) and in taking the drinks and supplements (as measured from the compliance calendar and pill count). Baseline characteristics between the groups will be compared by independent *t* tests for continuous variables and chi-square tests for categorical variables. Wherever possible, we will obtain endpoint measures from all withdrawals and include all randomized subjects in our final data analysis. All data will be checked for normality prior to analysis, and skewed data will be log transformed prior to analysis. Time, group and group-by-time interactions will be examined using generalized linear mixed models with random effects. Potential covariates to be included in the model will include: age, sex, race or ethnicity, changes in medication and change in habitual physical activity or diet. Multiple regression analysis will be used to investigate whether changes in lean tissue mass, muscle size, density and strength and a reduction in metabolic or inflammatory markers are predictive of any exercise-induced improvements in glycaemic control and insulin sensitivity. All data will be presented as mean ± standard deviation or 95% confidence intervals. The significance level will be set at *P* <0.05 or smaller if adjustments are made for multiple comparisons.

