#### Randomization and blinding

Following completion of baseline testing, participants will be randomized, stratified by sex and diabetes treatment (diet or oral hypoglycaemic agents), in blocks of four using a computer-generated random number sequence by an independent researcher. All research staff involved in the assessments will be blinded to the group allocation. The programme coordinator will be solely responsible for the distribution of the protein powder and vitamin D supplements. A flow diagram of the study protocol is outlined in Figure 1.

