### Sample size calculations

The sample size is based on the following power calculations from previously published studies of PRT in older adults (including those with type 2 diabetes) [10–12, 36, 38], and work of others that have assessed the independent or combined effects of protein, vitamin D and PRT on the outcome measures [16, 29, 53, 54]. It was estimated that 168 participants would provide 90% power (*P* <0.05 two-tailed test) to detect a 0.5% difference for the change in HbA_1c_ levels between the groups, assuming a conservative standard deviation of 1.1%. For insulin sensitivity, a sample size of 140 would be required to detect a 0.7 difference for the change in HOMA-2 insulin resistance between the groups at a power of 90%, assuming a conservative standard deviation of 1.2. To compensate for a projected 20% drop-out, a total of 202 participants will be recruited to the study and randomized 1:1 to the two groups (101 participants per group).

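### The stated primary model adjusts for neither the baseline outcome value nor diabetes treatment, a stratification factor; adding both costs only wording and should gain some power

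*Protocol article*

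**What the plan says.** Under Randomization and blinding, allocation is "stratified by sex and diabetes treatment (diet or oral hypoglycaemic agents"), in blocks of four. There are therefore two stratification factors, both known at baseline.

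Under Statistical analysis, the model is given as "Time, group and group-by-time interactions will be examined using generalized linear mixed models with random effects". On covariates the section says "Potential covariates to be included in the model will include: age, sex, race or ethnicity", and then adds changes in medication and changes in habitual activity or diet. One stratification factor (sex) is on this list; the other is not. Change in medication cannot stand in for it, because it is measured after randomisation. The baseline value of the outcome is not on the list either.

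Table 1 shows HbA1c and the HOMA-2 measures at baseline, 3 and 6 months, and Primary outcome measures defines the outcomes as changes. Sample size calculations is also framed on change: "It was estimated that 168 participants would provide 90% power" (P "<0.05 two-tailed test") for a "0.5% difference for the change in HbA_1c_ levels between the groups", "assuming a conservative standard deviation of 1.1"%.

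**The concern.** The three visits and the interaction terms suggest a model in which baseline HbA1c is one more outcome and the arms may differ freely at that visit. The treatment effect is then the arm difference in change from baseline. For a randomised trial this is a correct estimator but not the most precise one. The arms differ at baseline only by chance, and a model that uses this fact has a smaller variance.

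A change analysis also subtracts baseline with a weight of one, which over-corrects when the correlation is below one. An arm that starts high by chance tends to show a larger fall.

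Precision matters here because HbA1c power under the article's own inputs is below the stated 90% (see the working). Separately, a stratified design whose analysis names one of its two factors, and that one only as optional, does not match its own randomisation.

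**Working it through.** **Inputs from the article.** Difference 0.5; SD 1.1, read as the SD of change because the difference is a difference in change; two-sided 0.05; 202 randomised 1:1; 20% drop-out. Completers: 202 × 0.8 = 161.6, taken as 161.

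**Input not in the article.** ρ, the correlation between baseline and 24-week HbA1c. Assumed range 0.5 to 0.9.

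**The plan's own figure.** N = 4 × SD² × (1.960 + 1.282)² / d² = 4 × 1.21 × 10.507 / 0.25 = 203.4, so 204 evaluable. The stated 168 is not reproduced with a two-sided test; a one-sided 0.05 t-test gives exactly 168. That is a separate matter, but it sets the starting point: power is about 84% at 168 and about 82% at 161. HOMA-2 insulin resistance has no such shortfall: 4 × 1.44 × 10.507 / 0.49 = 123.5, so 124 against the stated 140.

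**What the stated model estimates.** In one simulated complete data set (160 people, three visits, random intercept, ρ = 0.5), the 24-week group-by-time estimate was −0.1359. The difference in mean change was the same, −0.1359. The two also agreed at ρ = 0.7 and 0.8.

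**Gain from baseline adjustment.** With equal variance σ² at both visits:
- Variance of change: 2σ²(1 − ρ)
- Variance after baseline adjustment: σ²(1 − ρ²)
- Ratio: (1 + ρ)/2

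So the SD of 1.1 becomes 1.1 × √((1 + ρ)/2). The standard error is SD × √(4/161), and power is approximately Φ(0.5/SE − 1.960). Unadjusted: SE = 1.1 × 0.1576 = 0.1734; 0.5/0.1734 = 2.884; power = Φ(0.924) = 82.2% (81.8% by noncentral t).

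| ρ (assumed) | Variance ratio | SD used | Power, normal | Power, noncentral t |
|---|---|---|---|---|
| no adjustment | 1.00 | 1.100 | 82.2% | 81.8% |
| 0.5 | 0.75 | 0.953 | 91.5% | 91.1% |
| 0.6 | 0.80 | 0.984 | 89.7% | 89.3% |
| 0.7 | 0.85 | 1.014 | 87.9% | 87.5% |
| 0.8 | 0.90 | 1.044 | 86.0% | 85.6% |
| 0.9 | 0.95 | 1.072 | 84.1% | 83.7% |

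**Chance imbalance.** If the arms differ by Δ at baseline, the expected change contrast shifts by −(1 − ρ)Δ, given that imbalance. At ρ = 0.7 the implied SD of HbA1c is 1.1/√0.6 = 1.42, so one standard error of the baseline difference is 1.42 × 0.1576 = 0.224. The shift is 0.3 × 0.224 = 0.067, against a target of 0.5. It averages to zero over randomisations.

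**Gain from diabetes treatment.** A main effect that is constant over time cancels from each person's change. In the simulated data the group-by-time standard error was 0.1671 with and without it. It helps only through a stratum-by-time term or in a baseline-adjusted model, and then only if it predicts change, or follow-up given baseline. The article does not say how strongly it does.

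**The case against.** The strongest reply has four parts.

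*The list is open.* The covariates are called potential, in a condensed article, and a fuller plan may add the missing terms. This stands as far as it goes: the final model may include both, and the article does not exclude them. But the article does set out a model and a list, and that list names one stratification factor without the other.

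*The structure is inferred.* The article does not say that baseline sits in the outcome vector with a free arm difference. The same words could describe a model of the 3- and 6-month values with baseline as a covariate. This also stands. The reading used here is the natural one, given the three visits and the change-based outcome and sample size, but it is a reading.

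*The gain rests on assumptions.* The correlation is not given, and at 0.8 to 0.9 the benefit is only two to four points. Nor is 1.1% labelled as an SD of change. If it were the SD of HbA1c itself, then at ρ = 0.7 the SD of change would be 1.1 × √0.6 = 0.852, and the unadjusted analysis would already have about 96% power with 161 completers. The equality with the change analysis is also exact only for complete data, while 20% drop-out is projected.

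*The stated analysis is valid and common.* This is correct; the point concerns efficiency.

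A reader might also infer three stronger things that the article does not support:
- That the model makes no use of baseline HbA1c. A change contrast does use it: relative to an analysis of follow-up alone its variance ratio is 2(1 − ρ), which is 0.6 at ρ = 0.7 and 0.4 at ρ = 0.8, with no gain at 0.5. Only the further step is forgone.
- That leaving out diabetes treatment makes the standard error too large. As a main effect in this model it makes no difference.
- That the baseline t and chi-square tests will choose the covariates. The article says only that baseline characteristics will be compared.

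**Conclusion.** The point holds as a worthwhile improvement at almost no cost; the planned analysis is not thereby wrong. The article stratifies on two factors and names one of them, optionally, for the model. It names no adjustment for the baseline outcome value.

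If baseline is the first repeated measure, 1.1% is the SD of change, variances are equal and 161 participants complete, baseline adjustment would lift HbA1c power from about 82% to about 91% at ρ = 0.5, 89% at 0.6, 88% at 0.7, 86% at 0.8 and 84% at 0.9. On these figures power reaches 90% only towards the low end of that range, so adjustment should not be counted on to repair the sample size by itself.

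For diabetes treatment no gain in power can be claimed from the article. The case for it is that the analysis should follow the stratified randomisation.

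**What to change.** State one primary model in advance. Either:

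- use the 12- and 24-week values as outcomes, with baseline value by time as a covariate, plus time, group by time, sex and diabetes treatment; or
- use all three visits with baseline means constrained equal across arms, plus time, group by time, sex and diabetes treatment, and the interactions of both stratification factors with time, since their main effects alone would add little.

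In either form, include sex and diabetes treatment unconditionally and name the 24-week contrast as primary. Apply the same form to the HOMA-2 outcomes.

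The cost is wording. The baseline outcome values and both stratification factors are already collected, and neither recruitment nor visits change. The model spends a few degrees of freedom, which is negligible at about 160 completers. The wording should be fixed before outcome data are seen by arm.

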#### Whey-protein drink and vitamin D supplementation

Participants randomized to the protein and vitamin D group will receive a 3-month supply of a whey-protein enriched powder and vitamin D supplements at their baseline testing appointment and again after 12 weeks. The protein powder will be provided in a single-use sachet form (OmniBlend, Campbellfield, Victoria, Australia). Participants will be instructed to add 150 ml of cold water to a calibrated ‘shake-and-take’ container and then add one sachet (powder) containing 20 g of whey-protein concentrate 80%, containing approximately 2.4 g of leucine, to the water, close the lid and shake vigorously for at least ten shakes and consume immediately. Participants will be instructed to consume one drink every morning before breakfast and one drink within two hours of each PRT session. Thus, they will consume a total of seven drinks per week, with an extra drink on each of the two training days during the first 8 weeks. This will increase to ten drinks per week when participants move to three sessions per week. This will raise the total supplemental protein dose from 20 g on non-training days to 40 g on training days. Each protein drink will provide approximately 335 kJ of energy, 2 g of lactose, 1 g of fat and 5 g of fibre. Participants will also be asked to take two 1000 IU capsules of Vitamin D_3_ (Ostelin, Melbourne, Victoria, Australia) every evening for the duration of the study. The goal of vitamin D treatment is to raise serum 25(OH)D concentrations to at least 75 nmol/l. All supplements and the protein powder will be provided free of charge.

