**Secondary outcome measures**				
Body composition	Dual energy X-ray absorptiometry total body and regional lean mass and fat mass, and bone density	×		×
	Peripheral quantitative computed tomography scan at 25% femur site	×		×
Biochemistry and hormonal measures	Routine biochemistry	×	×	×
	Serum 25-hydroxyvitamin D	×	×	×
Adipokines and inflammatory markers	Overnight fasted plasma collection	×	×	×
Blood lipids	Overnight fasted plasma collection	×	×	×
Blood pressure	Automated measurement	×	×	×
Muscle strength	Leg press and seated row	×		×
	Isometric knee extensor strength	×	×	×
Muscle function and balance	Timed up-and-go test	×	×	×
	Four-square step test	×	×	×
	30-second sit-to-stand test	×	×	×
Diabetes and other medication	Monthly reports	×	×	×
Health-related quality of life	Short Form (36) version 2 questionnaire	×	×	×
Cognitive function	CogState Brief Battery computerized tests	×	×	×

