## Discussion

This study will be the first randomized controlled trial in older adults with type 2 diabetes to investigate whether increased dietary protein achieved through the ingestion of a whey-protein drink combined with vitamin D supplementation can enhance the effects of PRT on glycaemic control, muscle mass and cardiometabolic risk factors. This is important because most current lifestyle approaches for the treatment of type 2 diabetes focus on general physical activity (typically aerobic training) and calorie restriction to manage body weight. While such approaches have been shown to improve glycaemic control, blood pressure and lipid levels and reduce weight and fat mass, they are often associated with a loss in lean tissue (muscle) mass [6, 7]. Given that skeletal muscle is the largest mass of insulin-sensitive tissue and the predominant reservoir for glucose disposal, there is a need to develop, evaluate and disseminate approaches that are safe and effective for optimizing muscle mass as well as glycaemic control and other cardiometabolic related risk factors in people with this disease, particularly older adults with type 2 diabetes who experience an accelerated loss in muscle mass with age [55].

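### Changes in medication, activity and diet, all measured after randomisation, are offered as covariates in the only between-group model of an intention-to-treat analysis and are not confined to a secondary analysis

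*Protocol article*

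**What the plan says.** All of the following is in the protocol article.

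- **Statistical analysis, principle:** "The primary statistical analyses will be conducted on an intention-to-treat basis".
- **Statistical analysis, model:** "Time, group and group-by-time interactions will be examined using generalized linear mixed models with random effects". No other between-group model is described for the outcomes.
- **Statistical analysis, covariates:** "Potential covariates to be included in the model will include: age, sex, race or ethnicity", and the same sentence continues with "changes in medication and change in habitual physical activity or diet". Nothing reserves the last three for a sensitivity analysis, and no unadjusted or baseline-only model is named as primary.
- **Whey-protein drink and vitamin D supplementation:** "This will raise the total supplemental protein dose from 20 g on non-training days to 40 g on training days", and "Each protein drink will provide approximately 335 kJ of energy". The control arm receives no powder or supplements.
- **Dietary habits:** 24-hour recalls at baseline, 12 and 24 weeks cover everything eaten and drunk. Nothing says that the sachets are left out.
- **Table 1:** "Diabetes and other medication" is a row under the secondary outcomes. The Secondary outcome measures text also lists diabetes medication as a secondary outcome, and names lipid-lowering and blood pressure medication among the other covariates and variables of interest.

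**The concern.** Randomisation protects a comparison that is adjusted for baseline variables. It does not protect one adjusted for something that happens afterwards and that the allocated arm can change. Such an adjustment can remove part of the effect that runs through the covariate. It can also create a spurious difference when the covariate and the outcome share an unmeasured cause.

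The strength of the case differs by covariate:

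- **Diet.** The Discussion describes the intervention as "increased dietary protein achieved through the ingestion of a whey-protein drink combined with vitamin D supplementation". A total-diet measure may therefore contain the treatment. If the sachets are left out, it may still record participants eating less of something else because of them.
- **Medication.** Participants' own doctors can alter prescriptions, and the monthly calls record this. The Screening and eligibility section asks for lipid-lowering and antihypertensive drugs to be held constant and does not mention glucose-lowering drugs there. If the covariate includes diabetes drugs, it may respond to glycaemia, and the plan would be using one variable as both outcome and adjuster.
- **Physical activity.** Both arms do the same training, so this is the weakest case. There is no placebo, however, so participants know their arm and could change other activity.

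At stake is whether the reported HbA1c and HOMA-2 differences answer the primary aim: training plus whey-protein and vitamin D against training alone.

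**Working it through.** No figure in the plan states the effect of this adjustment, so there is none to reproduce. The check has three steps.

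**1. How far the design itself can move a total-diet covariate**

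Inputs, from the intervention sections: one drink every morning and one per training session; two sessions a week for 8 weeks, then three for 16 weeks; 20 g of protein and about 335 kJ per drink.

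- Sessions: 8 × 2 + 16 × 3 = 64, which matches the stated 64.
- Drinks: 8 × 9 + 16 × 10 = 232 over 24 × 7 = 168 days.
- Protein: 232 × 20 / 168 = 27.6 g/day.
- Energy: 232 × 335 / 168 ≈ 463 kJ/day.

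These are averages at full compliance, in one arm only. A recall that includes the drinks therefore differs between arms by construction, unless participants compensate elsewhere.

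**2. What adjustment does to the group effect**

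In a linear model of change:

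adjusted effect = total effect − (effect of arm on covariate) × (slope of outcome on covariate, given arm)

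The document gives neither factor in the product. As an illustration only, take a total effect of −0.50 HbA1c points, with assumed shifts in SD units of the covariate and assumed slopes per SD:

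| Arm shift (SD) | Slope per SD | Adjusted effect |
|---|---|---|
| 0 | any | −0.50 |
| 0.5 | −0.2 | −0.50 + 0.10 = −0.40 |
| 0.8 | −0.3 | −0.50 + 0.24 = −0.26 |
| 0.5 | +0.2 | −0.50 − 0.10 = −0.60 |
| 0.8 | +0.2 | −0.50 − 0.16 = −0.66 |

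The estimate can shrink or grow. Bias also arises when the covariate has no effect of its own. With a shared unmeasured cause (assumed loading 0.5 on each), the apparent slope is 0.5 × 0.5 = 0.25. A shift of 0.25 to 0.8 SD then gives −0.56 to −0.70.

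**3. Whether the form of entry matters**

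It does. The group-by-time term compares within-person change between arms. A covariate with one value per person, entered only as a main effect, cancels when a person's visits are differenced. Simulation agrees. The inputs are assumed: an effect of −0.50 acting wholly through diet, an arm gap of 28.6 g/day (the week 9 to 24 value, 20 + 3 × 20/7), SD 25 g/day, 4,000 participants, three visits and a random intercept.

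- No diet covariate: group-by-time −0.495.
- Change in diet as a main effect only: −0.495.
- Diet as a time-varying term: about 0.

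A further simulation of a wholly diet-mediated effect gave −0.56 both without the covariate and with it as a main effect only. It gave about −0.04 when the covariate was time-varying, interacted with time, or used in a change-score analysis of covariance. Full mediation is an extreme case, chosen to separate the model forms; it is not a forecast.

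**The case against.** The best defence has four parts.

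1. **The covariates are only potential.** This stands: any bias arises only if they are used. But the sentence places them in the model, and no primary analysis is kept clear of them. Leaving the choice open also allows it to be made after results are seen.
2. **Habitual diet may mean background diet without the sachets.** The Background separates a supplement from usual eating habits, so this reading is fair. A reader might infer that change in diet simply is the intervention, but the document does not establish that. What remains is that compensation for the drinks would still be a consequence of allocation, and that the recall as described does not exclude them.
3. **Medication may mean lipid-lowering and blood pressure drugs.** The Secondary outcome measures text names those among the covariates and variables of interest, and keeps diabetes medication as an outcome. The Statistical analysis section says only medication, so the point about drugs that follow glycaemia is conditional on diabetes drugs being included.
4. **A change score entered as a main effect does not disturb group-by-time.** This is correct, as step 3 shows. The harm depends on a model form that the article does not state.

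A wish to control confounding is a weaker defence. Randomisation already balances confounders in expectation, and adjusting for later variables can undo that.

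**Conclusion.** The point holds in conditional form. The plan permits three post-randomisation covariates in its only between-group model while promising an intention-to-treat analysis. If they enter as time-varying terms, interact with time, or are used in a change-score model, the group effect does not estimate the total effect of assignment, insofar as allocation moves them or they share causes with the outcome in an arm-dependent way. The case is strongest for diet, conditional for medication and weakest for physical activity.

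A reader might go further and conclude that the primary comparison will be biased, that the effect will be understated, or that power will fall by a definite amount. The document supports none of these. It leaves the use and form of the covariates open, and gives no covariate SDs, arm shifts or slopes. The only size that follows from the document is the designed supplement difference of about 27.6 g/day of protein and 463 kJ/day at full compliance. The adjusted HbA1c effects shown in the check rest on assumed inputs and indicate only that the error can run in either direction.

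**What to change.** In the Statistical analysis section, limit covariates in the primary and other intention-to-treat models to baseline variables, for example age, sex, the diabetes-treatment stratum used in randomisation, and race or ethnicity. Delete the three change covariates from that model. Report changes in medication, physical activity and diet by arm. If an effect adjusted for any of them is wanted, present it as a labelled sensitivity analysis that states the estimand, which drugs are counted and whether the sachets are part of the diet measure.

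The cost is a sentence or two of text. It needs no new data and places no burden on participants.
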